### Secondary outcomes

Muscle strength. The 1-repetition maximum (1-RM) for leg press will be used to determine changes in lower extremity muscle strength. The 1-RM test is a safe and effective means of evaluating strength, even in geriatric populations that have never lifted weights before [59,60], in BCS who have strength trained [61-63], and in cancer survivors with lower-extremity lymphedema [64]. We have evaluated maximal strength using the 1-RM technique in 3 studies of BCS (age range: 35–89 yrs) with no adverse events. The 1-RM test will be conducted according to established protocols [52]. We will also consider changes in functional leg strength using the timed chair stand test (see PPB) so that strength changes can also be interpreted in a clinical context [65].

Postural Stability. Computerized dynamic posturography (CDP; Clinical Research System, Neurocom Intl, Inc.) measures postural stability and is used to identify objective patterns of balance problems consistent with neuropathy, vestibular loss, and CNS disorders that contribute to fall risk [66]. The test protocol used in this study is the sensory organization test (SOT), which systematically removes or alters useful information to the patient’s vision or support surface to create sensory conflict situations. These conditions isolate vestibular control of balance, as well as stress adaptive sensory reweighitng by the central nervous system. Equilibrium scores are determined for each condition based on maximum forward-backward postural sway. The weighted average of the scores of all sensory conditions characterizes the overall level of performance as a composite equilibrium score. Sensory ratios are calculated by comparing individual equilibrium scores in specific conditions to identify impairments of individual sensory systems including the vestibular, somatosensory, and visual systems. Equilibrium scores and sensory ratios range from 0–100, where 100 = perfect stability and 0 = an inability to maintain balance and a fall. In this study, we are interested in the composite equilibrium score and also the somatosensory and vestibular sensory ratios, since the latter may show differential effects of the 2 interventions on physiologic systems affected by cancer chemotherapy that impair stability (i.e., neuropathy and vestibular impairment). Test-retest reliability of composite equilibrium scores ranges from 0.72 - 0.93 [67].

Physical Functioning will be measured by the Physical Performance Battery (PPB) [68]. The PPB consists of 3 timed performance tests: 5 repeated chair stands, standing balance, and gait speed over 4 meters. We will consider the time scores of the chair stand test and gait speed separately to examine them as clinical measures of strength and postural stability that might mediate fall risk for Aim 2 (see Analysis Plan). Though not a primary aim of our study, the transformed PPB score can be used to evaluate the effect of the intervention on overall physical function, which would be an important additional benefit of the exercise programs. In older adults, low scores on the PPB are significantly associated with subsequent mobility disability, ADL disability, hospitalization, admission to a nursing home, and mortality [68-71]. The PPB is reliable, sensitive to change [72] and has established norms. Higher scores indicate better physical functioning. Reliability of the PPB is high with intraclass correlation coefficients ranging from 0.88-0.92 for individual tests and the composite score [72].

Flexibility may improve in the control group, so we will measure flexibility in all groups using the standardized Chair Sit and Reach Test for lower body flexibility and Back Scratch Test for upper body flexibility [73]. These tests are designed for older adults with demonstrated validity and reliability in older adults (test-retest 0.95-0.96) [73].

### Descriptive variables

Demographic information, including age, education, income, and others will be measured at baseline by a questionnaire developed for this study. In addition, stage of prior cancer diagnosis, type and dates of cancer treatments, additional adjuvant treatments (i.e., hormone manipulation therapy for breast cancer), presence of other chronic conditions, current medications and health habits will be measured. Clinical measures of weight and height will be made. Updated information will be collected at subsequent visits.

Presence of chronic medical conditions that affect physical functioning will be measured by the Functional Comorbidity Index, which is a self- administered 18-item scale and has stronger associations with SF-36 physical function (R [2]=0.29) than other comorbidity indices [74]. Indivdual item responses from this questionnaire will also be used to inform the exercise instructor about medical conditions that might affect participants’ physical ability to exercise.

Fear of falling may impact a participant’s confidence that she can safely engage in a study exercise program. This factor may also change across the intervention. Though this is not a major outcome in this study, it may provide important information about the population and intervention. The Survey of Activities and Fear of Falling in the Elderly (SAFFE) [75] has 11 items representing activities of daily living associated with fear of falling, mobility, and social activities. The SAFFE score is the average of item responses, with higher scores indicating greater fear of falling and has high internal consistency (intra-class correlation coefficient: 0.91) [75].

Exercise outside the exercise intervention could affect the fall and function outcomes of the study. The CHAMPS Physical Activity Questionnaire for Older Adults, a valid and reliable instrument [67], will be used to measure outside physical activity across the course of the study.

Adherence (% of prescribed sessions completed) is tracked from attendance logs recorded by the exercise instructor. Adherence data is used to describe the dose of exercise received by participants. It is expected that women will occasionally miss classes due to travel, illness, or other reasons. However, it is important to count missed classes to get an accurate estimate of received (exercise) dose and to generalize our findings.

### Data analysis plan

The univariate distribution of each variable will be examined to check for departure from normality and outliers [76]. For each analysis described below, each subject will be analyzed according to the group to which she was randomly assigned and regardless of missing data (i.e., intention to treat). Medical treatment changes and cancer recurrence during the study will be tracked and used to describe the sample and document why participants may not have completed the study. In the unlikely event of a large subgroup, these data could be used for exploratory sub-group analysis to suggest directions for future research. Age, cancer type (breast or other), and time since cancer treatment completion, will be included as covariates in all analyses.

A negative binomial regression model will be used to test the efficacy of tai chi and strength training (versus stretching control) in reducing the total number of falls per participant that occur during the intervention period (from baseline to 6 months). Negative binomial regression is preferred over Poisson regression for modeling the count data because of the overdispersion that is common with actual research data [40,77]. Intervention type will be entered into the model as 2 dummy vectors, with the reference group being the control group. Fall rates for participants who drop out of the study will be adjusted by accounting for their exposure time within the study timeframe. A significant incidence rate ratio (IRR) less than 1.0 for the dummy vector representing tai chi and/or strength training would provide support for the hypothesis that the respective intervention reduced the rate of falls compared to the control group (controlling for covariates).

Muscle strength and postural stability will be tested as potential mediators of the relationship between the exercise interventions and falls. We propose that strength and stability will mediate the effect of each intervention on falls because both constructs will be affected by each intervention and are major risk factors for falls. Though we do expect stronger effects of strength training on strength and of tai chi on stability, how each program specifically reduces falls is uncertain, particularly in women treated for cancer. Mediation analyses will be conducted in a structural equation modeling framework (SEM) implemented in Mplus 7.0. A manifest model will be tested with dummy vectors representing tai chi and strength training as exogenous variables, strength and stability (difference score from baseline to 6 months) as endogenous variables (mediators), and number of falls that occurred from baseline to the end of the intervention as an endogenous variable (outcome). The SEM framework allows for the assessment of indirect (mediating) effects with mixed distributional models, in this case Guassian for both mediators and negative binomial for the outcome. Support for mediation will be determined by assessing the magnitude and significance of the indirect effects (standard errors calculated with the multivariate delta method [78]) from the treatment variables to number of falls through changes in strength and stability. Additional mediation analyses will be conducted replacing composite SOT score as the measure of stability with SOM and VEST scores, and replacing maximal knee extensor force (Nm) and composite SOT with clinical measures of strength (PPB chair stand) and dynamic stability (gait speed).

The persistent effects of the intervention on fall outcomes after formal training stops will be evaluated with a piecewise intent-to-treat negative binomial regression model with the change point occurring at 6 months. Of particular interest is whether the IRRs for the treatment groups differ after the change point. In addition, the moderating effect of participation in an exercise program following the end of the intervention will be examined. Specifically, exercise programs engaged in for least 50% of the follow-up period will be categorized and dummy coded (e.g., infrequent participation versus regular participation). These variables will be entered into a negative binomial regression model along with the product of these dummy vectors and treatment (i.e., interaction effects). Significant interaction effects indicate that continued participation modifies the effect of the intervention on fall rate. With this analytic approach we will be able to determine whether the benefits of the exercise interventions persist with and without continued participation in an exercise program, and whether control participants who begin programs similar to the intervention programs show improvements on the fall rate outcome.

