### Power and sample size

The sample size is powered to address the primary study aim to reduce falls. In older adults, 30% of community-dwelling elders are likely to fall within 1 year [37] and Li and others have reported a reduction in fall risk of 47% from 3 [38] or 6 [22] months of tai chi exercise. This effect size provided a realistic estimate of the expected reduction in fall risk and was used as the basis for power analyses. The required sample to test the primary hypotheses in a negative binomial regression model [39] was determined with the following assumptions:, alpha=.05, 25% shared variance (R [2]=.25) among the dummy vectors representing treatment, and an overdispersion parameter (Phi) of 2.5. Under these assumptions a sample size of n=342 (n=114 per group) will provide 80% power to detect at least a 47% reduction in the fall rate over 1 year by being in the 2 experimental groups (tai chi and strength training) versus the control group. These estimates were generated using PASS 2008 [40]. To protect against an estimated attrition of 25% during the intervention period, 143 participants will be randomized per group (total sample size: N=429). The attrition estimate is based on attrition rates in yearlong studies of weighted vest strength training in BCS [41] and slightly higher than what has been observed in 1-year studies of older women without cancer participating in tai chi exercise [42,43] (19%-24%) or resistance exercise (24%) [43].

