### Study interventions

Participants in each study group will attend supervised 1-hr classes, twice weekly for 6 months. It is expected that women with mixed employment status will enroll in the study so daytime and early evening classes will be offered. At each site, a certified exercise instructor trained by the study team will lead classes. Each intervention minimizes reliance on expensive equipment and uses simple, easily performed exercises based on functional movements. It is difficult to precisely equilibrate the total volume (intensity and duration) of exercise performed between experimental groups because the nature of each modality is so different. Both will be matched as closely as possible in progression from the low to high end of the range for moderate intensity. Instructors will work with the study investigators and project director on a monthly basis to refine individual participant efforts based on individual tolerance and to adjust their training progression.

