## Measures

### Primary outcome

Falls: In this study, a fall is defined as unintentionally coming to rest on the ground or at some other lower level, not as a result of a major intrinsic event (e.g., stroke or syncope) or overwhelming hazard [57]. Falls will be assessed retrospectively at baseline through 6-month recall to characterize the sample and check for equality of randomization. Falls will be assessed prospectively during the study by monthly reports completed through a web portal or returned by postal and/or electronic mail, methods proven successful in our 2 previous studies and by others, including [name] [3,4,22,58]. In our recently completed observation study of BCS (N=58), we obtained 98% of monthly fall reports over 6 months [3]. If a participant indicates a fall she will then be asked to detail any injury that resulted from each fall. A fall will be considered “injurious” if it results in fractures, head injuries, sprains, bruises, scrapes, or serious joint injuries, or if the participant seeks medical care [57]. Of interest in the study are the number of falls, the number of injurious falls, and medical care resulting from a fall during the intervention period.

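### Baseline six-month falls are collected but left out of the covariates fixed for the fall models, which gives up precision whenever prior falls predict later falls.

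*Protocol article*

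**What the plan says.** Under Measures, Primary outcome, the protocol article states the purpose of the baseline fall history: "Falls will be assessed retrospectively at baseline through 6-month recall to characterize the sample and check for equality of randomization". No other use is given for it.

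The Data analysis plan fixes the adjustment set for every analysis: "Age, cancer type (breast or other), and time since cancer treatment completion, will be included as covariates in all analyses". The primary analysis is a negative binomial regression of the "total number of falls per participant that occur during the intervention period (from baseline to 6 months"), and "Intervention type will be entered into the model as 2 dummy vectors, with the reference group being the control group". The same section plans a piecewise negative binomial model, with a change point at six months, for the follow-up period.

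Power and sample size assumes "an overdispersion parameter (Phi) of 2.5" and "25% shared variance (R [2]=.25) among the dummy vectors representing treatment".

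**The concern.** Baseline falls are the outcome itself, measured before randomisation over a window as long as the primary outcome window. The plan expects overdispersed counts and chooses its model for that reason. Stable differences between women in fall-proneness are one natural source of overdispersion, and a prior fall count can capture part of them. The plan already accepts covariate adjustment, so leaving this variable out is a choice about which covariates to use, not a decision against adjusting.

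Two things are at stake. The first is the width of the intervals for both incidence rate ratios. The second is chance imbalance in prior fallers: checking for it does not remove it from the estimate, whereas adjustment does so to the extent that prior falls are prognostic.

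This is not a detail left to a fuller document. The article states a specific covariate list for all analyses and a different, limited use for baseline falls. An analysis plan that added the variable would depart from this text.

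**Working it through.** **The plan's own figures.** The article gives no figure for the gain from adjustment. Its R² of 0.25 is described as variance shared among the treatment dummies. With three equal groups the two dummies correlate at -0.5, and (-0.5)² = 0.25, so that term credits nothing to prognostic covariates. The stated 342 evaluable women could not be reproduced from the printed inputs. With all of them kept and a two-sided test, it needs a control mean of about 0.85-0.99 falls per year, which the article does not give. So 342 is not shown to be wrong, and it serves below only as a scale.

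**Inputs**
- Rate ratio 0.53 (47% reduction) and Phi = 2.5, from Power and sample size.
- Outcome window of six months, from the Data analysis plan.
- Baseline window of six months, from Primary outcome.
- Assumed: Phi is a variance-to-mean ratio, Phi = 1 + kμ, with gamma frailty of variance k and control mean μ. The article does not say which period Phi refers to, so both readings are shown.
- Assumed: the degree to which a woman's frailty persists from the baseline window to the trial window.

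**Formula at full persistence, perfect recall.** With n women per arm, one arm against control:

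- Unadjusted: Var(log IRR) = (1/n)[1/μ + k + 1/(0.53μ) + k].
- Given a baseline count with mean μ from the same frailty, each k becomes k/(1 + kμ).

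Multiplying through by μ and writing x = kμ for six months:

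ratio = [1 + 1/0.53 + 2x/(1 + x)] / [1 + 1/0.53 + 2x], with 1/0.53 = 1.887.

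| Reading of Phi = 2.5 | x | Ratio | Women needed to match 342 unadjusted |
|---|---|---|---|
| Applies to 1 year (yearly kμ = 1.5) | 0.75 | 3.744/4.387 = 0.853 | 342 × 0.853 ≈ 292 |
| Applies to 6 months | 1.5 | 4.087/5.887 = 0.694 | 342 × 0.694 ≈ 238 |

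That is a variance reduction of about 15% or 31%, and it is the upper end.

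**Rare falls.** At 0.15 falls per six months with k = 1 to 2.5, x = 0.15 to 0.375. The ratio is 3.148/3.187 = 0.988 to 3.432/3.637 = 0.944, a gain of about 1-6% even at full persistence.

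**Partial or no persistence.** Simulation at 114 per group gave these model-based variance ratios, adjusted over unadjusted:

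| Frailty correlation, baseline to trial | Variance ratio |
|---|---|
| 0 | 1.003-1.005 |
| 0.5 | 0.95-0.97 |
| 1 | 0.74-0.94 |

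The runs were small (200-400 per setting), and some fits at the lowest rates did not converge. The table gives orders of magnitude, not exact values.

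**Recall error.** With 107 per arm, 0.5 falls per six months, frailty variance 1.5 and full persistence, the median SE of the log IRR fell from 0.287 to 0.266 with complete recall and to 0.274 if only 60% of prior falls are recalled. Poor recall shrinks the gain but, in that setting, does not remove it.

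**The case against.** The strongest reply is that nothing here is an error. The plan prespecifies a valid, covariate-adjusted comparison of randomised groups, and which prognostic covariates to choose is largely a design judgement. That stands as to validity: the issue is efficiency, not bias.

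A second reply is that the documents do not show that prior falls predict later falls in these women. That also stands. The Data analysis plan says only that overdispersion is common in real data, and the article does not rank prior falls above its three chosen covariates. The eligibility criteria even give a reason to doubt full persistence. Women may enter just over three months after chemotherapy, so for some the six-month recall window overlaps treatment. This limits the size of the gain. It does not reverse the argument, because an uninformative covariate costs almost nothing.

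Stronger readings are tempting but not supported:

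- **A single gain of 10-16% more women.** That needs full persistence and, for example, one fall per year at frailty variance 1.5. It implies that 1 - 2.5^(-1/1.5) ≈ 46% of women fall in a year, against the 30% cited under Power and sample size. Matching 30% at that frailty variance means about 0.24 falls per six months, where simulation put the gain at about 2-3% even at full persistence.
- **The trial is already short of its stated power.** One could take 143 × 0.75 ≈ 107 per arm, below the 114 required. But the plan keeps dropouts in the model with their exposure time, and 342 is not shown to be wrong.
- **The model must also allow for clustering by class.** All programs are class-based, but the article gives no intraclass correlation or class size, and a condensed article commonly leaves such variance handling to the full plan.
- **The balance check should go.** Describing baseline falls by arm does no harm and does not preclude adjustment.

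**Conclusion.** The point holds as a missed, nearly free gain in precision. Baseline falls are collected, their stated use is limited to description and a balance check, and the covariate list for all analyses omits them. The randomised comparison remains valid without the change.

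No single size should be attached. The supportable range for the variance reduction runs from about 0% (no persistence), through about 3-5% (frailty correlation 0.5), to about 15-31% (full persistence, Phi 2.5 read over one year or six months). Rarer falls and incomplete recall pull it down. The range rests on a gamma frailty model, on Phi as a variance-to-mean ratio, and on a persistence that the documents do not report. Against it stands a variance loss of about 0.5% or less if the covariate turns out to be useless.

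**What to change.** Add the baseline six-month fall count to the covariates in the Data analysis plan, for both the primary negative binomial model and the piecewise follow-up model. Fix the functional form in advance, for example log(1 + falls), and state a rule for missing recall. Make the change before any unblinded data are seen. In Primary outcome, add adjustment to the stated purposes of the baseline recall; the descriptive use and balance check can stay.

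The cost is a change of wording and one extra parameter in each model. No new data, visits or participants are needed.

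### Aim 2: the path from strength or stability gain to falls is not randomised, and its stated covariates omit likely common causes that the trial measures

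*Protocol article*

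**What the plan says.** The Data analysis plan section sets one covariate list: "Age, cancer type (breast or other), and time since cancer treatment completion, will be included as covariates in all analyses". For Aim 2 it then describes a structural equation model: "A manifest model will be tested with dummy vectors representing tai chi and strength training as exogenous variables". The mediators are baseline-to-6-month difference scores in strength and stability, and the outcome is the fall count over the same period (negative binomial). The rule for a mechanism is: "Support for mediation will be determined by assessing the magnitude and significance of the indirect effects", with delta-method standard errors. No further covariate is named for this model.

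Under Descriptive variables, "Presence of chronic medical conditions that affect physical functioning will be measured by the Functional Comorbidity Index". The article adds that this index "has stronger associations with SF-36 physical function (R [2]=0.29) than other comorbidity indices" and that its item responses "will also be used to inform the exercise instructor about medical conditions that might affect participants’ physical ability to exercise". The same section measures outside physical activity with the CHAMPS questionnaire, on the ground that such exercise may influence both falls and function. It also records weight, height, and the type and dates of cancer treatment. None of these is given a place in the Aim 2 model.

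**The concern.** Three covariates are enough for arm contrasts, because the arms are randomised. A woman's own gain in strength or stability is not. Within an arm, the association between gain and falls is observational, and anything that affects both will be read as part of the mechanism.

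The article makes such common causes plausible:

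- The Sample section deliberately admits women with chronic conditions.
- The Study interventions section has instructors adjust effort and progression to what each woman tolerates.
- The Background links muscle wasting, neuropathy and vestibular damage after cancer treatment to poor balance and falls.
- The reason given for measuring outside exercise comes close to the definition of a mediator-outcome confounder.

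Mechanism is the trial's stated secondary aim. An indirect effect that partly reflects being healthier could misinform the choice between programs, and a masked one could hide a real mechanism.

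**Working it through.** The article gives no power, effect size or error rate for Aim 2, so there is no figure of its own to reproduce. The check asks what the stated model would report if the true mediated effect were zero.

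**Inputs from the article**

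- 114 women per arm for analysis, or 143 × 0.75 ≈ 107 per arm after the planned 25% attrition.
- Planned fall rate ratio of 0.53, so ln(0.53) = -0.635.

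**Assumed inputs (the article gives none)**

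- a: arm effect on the mediator, 0.5 SD.
- r: size of the within-arm correlation between comorbidity and gain, with women with more comorbidity gaining less.
- RR: fall rate ratio per SD of comorbidity.
- Control mean: 0.3 to 1.0 falls per 6 months.

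**Step 1: large-sample bias.** With comorbidity omitted and no causal mediator effect, the mediator coefficient in the falls model is b = -r × ln(RR). The false indirect effect is a × b, and the false indirect incidence rate ratio (IRR) is exp(-a × r × ln(RR)).

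| r | RR | a × r × ln(RR) | False indirect IRR | Share of planned log effect (÷ 0.635) |
|---|---|---|---|---|
| 0.1 | 1.2 | 0.009 | 0.99 | 1% |
| 0.2 | 1.5 | 0.041 | 0.96 | 6% |
| 0.3 | 1.5 | 0.061 | 0.94 | 10% |
| 0.3 | 2.0 | 0.104 | 0.90 | 16% |
| 0.5 | 2.0 | 0.173 | 0.84 | 27% |

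**Step 2: false support on the planned delta-method test.** Simulation with 300 trials per scenario and 114 per arm. The direct arm effect on falls was 0.53 and the indirect effect zero, and three inert covariates were always included. The rates count significant results in the expected direction, where the nominal rate is 2.5%.

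| r | RR | Comorbidity omitted, over control means 0.3 to 1.0 |
|---|---|---|
| 0 | none | 1% to 2% |
| 0.2 | 1.5 | 4% to 5% |
| 0.3 | 1.5 | 4% to 13% |
| 0.3 | 2.0 | 14% to 33% |
| 0.5 | 1.5 | 14% to 33% |
| 0.5 | 2.0 | 40% to 69% |

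Monte Carlo error is up to about 3 points. Some negative binomial fits gave convergence warnings, so the rates are approximate.

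**Step 3: comorbidity added to both equations.** The indirect IRR returns to 0.99 to 1.01, and false support is 0% to 1.7% in every scenario.

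**Step 4: second configuration.** This used 1,500 trials, 107 per arm, a control mean of 0.5, dispersion 1.2 and both mediators in the model. With r = 0.3 and RR = 1.5 the false indirect IRR was 0.94 to 0.95, and false support was 8% against 1.4% with adjustment. The slightly smaller bias is expected. If the two mediators are related only through comorbidity, b = -r × ln(RR) / (1 + r²) = -0.3 × 0.405 / 1.09 = -0.112, and exp(-0.5 × 0.112) = 0.946.

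**Step 5: opposite sign.** If women with more comorbidity gain more (correlation +0.15, RR = 1.5), the indirect IRR is exp(0.5 × 0.15 × 0.405) = 1.03. Simulated false support in the expected direction falls to 0.2%, and a real mechanism would be understated.

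**The case against.** **The list may not be exhaustive.** The covariate sentence says what every model must contain and does not forbid additions. This is also a condensed article, so a fuller plan may add covariates. That is fair. Still, the article sets out the Aim 2 model in some detail, with its exogenous variables, mediators, outcome and decision rule, and adds nothing for the non-randomised path. The point concerns the model as stated. A reader might also infer that the extra measures serve only to describe the sample. The article does not say that: comorbidity items also inform instructors. It states no use of them in the Aim 2 model.

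**Training load varies in one arm only.** Vest weight applies only to strength training, tai chi uses body weight, and controls stretch seated or lying. With the -0.3 correlation confined to the strength arm and RR = 1.5, the false indirect IRR is 0.98, and two-sided false support is 3.0% against 2.0% without confounding. This limits a pure load argument. It does not remove the point, because instructors adjust effort and progression to tolerance for participants generally. The size of any correlation in the other arms remains an assumption.

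**The direction is not established.** A reader might infer that the bias must run towards a false mechanism, or that the quoted R² of 0.29 demonstrates it. Neither follows. The mediators are difference scores, so a stable effect of comorbidity on level cancels, and 0.29 refers to level of function. Women who start lower may have more room to gain.

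**The size can be overstated.** Joint significance of both component paths would give 16% false support, or 30% for at least one of the two target paths (10% even when adjusted), but the plan uses the delta method. At a correlation of 0.15 and RR = 1.5, the delta test gives 3.0%. The plan also weighs magnitude, and 0.94 is only about 10% of the planned log effect. Adjustment for age, exclusion of contraindicating conditions and physician clearance may each weaken the links further. All of this stands as a limit on size.

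**Conclusion.** The point holds as a correctable weakness in a secondary aim. Only the arm is randomised in the Aim 2 model, and the stated covariates omit comorbidity and outside activity, which the trial measures and treats as relevant to function. Bias arises only if these variables predict change in the mediators within arm as well as falls, and its sign follows the sign of the link with change.

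Under moderate assumed links the false indirect effect is modest and false support exceeds the nominal rate. Under weak links both are minor, and under strong links the error rate is serious. The documents do not show which case applies, so they support saying that the stated model can mislead on mechanism, and not that it will. The effects of arm on falls and of arm on the mediators are not touched.

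**What to change.** For Aim 2 only, add these to both the mediator equations and the falls equation:

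- the baseline Functional Comorbidity Index;
- baseline CHAMPS outside activity;
- body mass index from the measured weight and height;
- cancer treatment type, in the form collected.

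State that the gain-to-falls path is observational and conditional on these covariates, and that unmeasured confounding remains possible. The primary model can stay as it is.

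The cost is a sentence or two in the plan and a few degrees of freedom. The article does not say outright that the comorbidity index and CHAMPS are taken at baseline, so this needs confirming. Baseline values are the ones to use, since later activity may itself respond to the assigned program. Chemotherapy regimen should not be relied on: the article lists only the type and dates of treatments.
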